**Fig. 1 fig1:**
[figure not shown]
Overview of study design.

### Randomization and blinding

3.3

Cohorts of 24–46 (12–23 per group) participants are recruited into the study and undergo group assignment via simple randomization using a random number generator. Enrollment concludes at their follow-up visit within 6 weeks after the end of their 8-week reporting (intervention) period. To conserve scientific integrity and minimize the introduction of researcher bias, research assistants conducting study visits are blinded to participant group assignment (single-blind). Allocation concealment is maintained by limiting access to the random sequence until the moment of assignment, and a new random sequence is generated for each cohort. Randomization assignment is completed by the study coordinator using a list of anonymized study IDs for that cohort. To prevent experimenter bias, research staff providing the intervention will not be allowed to run follow-up study visits for participants in any cohort to which they have delivered an intervention. Participants unable or unwilling to complete an in-person follow-up visit are provided with the option to complete the questionnaires virtually; this policy was implemented to optimize retention given the ongoing global pandemic and anticipated challenges with in-person follow-up visits.

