### Study design

3.2

Baseline visits conducted at Helfgott Research Institute include confirmation of eligibility criteria, informed consent, study questionnaires, and sEMG collection for 20 gait cycles. Follow-up visits include all steps except repeated informed consent. All participants receive an email containing the informed consent document after baseline visit. Within 16 weeks of baseline visit completion, participants are randomized to either an 8-week MBI and treatment as usual (MBI + TAU) or TAU-only group to be completed in parallel cohorts. Both groups are asked to refrain from changes to their current treatment plan whenever reasonable (i.e., to avoid self-directed changes in treatment such as starting a new supplement) and to report any medically necessary (i.e., physician-recommended or -implemented) changes made during study enrollment. All study participants receive a copy of a pain education handout, “Understanding Pain,” at the time of intervention initiation as an effort to reduce the disparity upon health education [42]. This handout is provided publicly by the Oregon Pain Management Commission. Participants in both groups are asked to report daily pain levels using a Visual Analog Scale (VAS) administered via text message or email as preferred per participant.

Treatment as usual was chosen as the control condition for this experiment, as experts recommend using TAU control groups in studies of MBIs based on evidence from other RCTs conducted in this realm [43]. MORE has not been studied in the context of LR, and no gold standard has been identified as an active control for MORE in this subpopulation; therefore, TAU was deemed as appropriate for this study design. The control group undergoes TAU over 8 weeks of parallel group comparison and starts their 8-week enrollment period on the same day as the experimental group. Participants assigned to the TAU control group are offered to join a MORE program be delivered after the data collection period of the trial has ended. Our study team offered this option as we anticipate a benefit from MORE in the management of lumbosacral radiculopathy. A study flowchart can be seen in Fig. 1.

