### Intervention

3.4

Participants randomized to the intervention group undergo an 8-week mindfulness training program as instructed by the “MORE for the Treatment of Chronic Pain” manual. The intervention consists of weekly virtual sessions during which participants are asked to follow along with a guided meditation read by a trained MORE instructor and to engage in reflection and discussion exercises with other study participants. MORE instructors are trained via a two-day intensive workshop, the only education in MORE available at the time of this publication. The planned MORE instructor for this trial has delivered other mindfulness interventions such as Being Present 2.0 [44] and is certified in delivery of Cultivating Emotional Balance. All sessions are conducted using the virtual conference platform Zoom®; session topics are outlined in Table 2. The main techniques of MORE, mindfulness, reappraisal, and savoring, are delivered in session 1, 3, and 4. Mindfulness within MORE prompts participant awareness of pain oriented attention; reappraisal asks participants to “consider new ways of thinking about a stressful situation; ” and savoring encourages participants to direct attention towards rewarding experiences [45].

**Table 2 tbl2:** MORE session topics.

Session 1	What is Pain and Why Can Mindfulness Help?
Session 2	Automaticity in Chronic Pain
Session 3	Mindful Reappraisal
Session 4	Mindful Savoring
Session 5	Relationship between Pain and Unhealthy Coping Habits
Session 6	The Stress Response to Pain
Session 7	Pain and Thought Suppression
Session 8	Review and Discussion of Maintaining a Mindfulness Practice

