### Power and sample size calculations

3.7

Using results of Braden et al., a standard deviation of 8.3 points for the Oswestry Disability Index was used for effectiveness of mindfulness-based stress reduction in LBP patients [79]. An effect size of Cohen's *d* = 0.83 was calculated when using the reported minimal clinically important difference of a 10-point change [57,80]. Effect sizes ranging from 0.5 to 1.1 have been found previously for mindfulness interventions using outcome measures of pain and physical function in mechanically and neurologically derived LBP. The large effect sizes powered for in this study are considered acceptable due to the large effect sizes found in studies using MORE with multiple outcomes measures [35,36,41]. Using the GPower program (version 3.1.9.4) for *a priori t*-test sample size calculations using *alpha* = .05 yields 80% power to detect an effect of treatment of size *d* = 0.83, with a sample size of 48 participants. When adjusting for an expected retention rate of 80%, a total proposed sample size of 60 participants is required (*n* = 30 per group).

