### Statistical analytical plan

3.8

Participant descriptive information collected at baseline, including demographics, pain characteristics, physical function, QoL, depression, and trait mindfulness will be reported as mean (SD) or number (percent), as appropriate, for each study group. Likewise, changes from baseline to follow-up of each outcome measure will be reported as mean (SD) for each group.

*A priori* analytical modeling has been developed based on primary and secondary outcome measures and established relevant covariates. Relevant covariates (according to priority) include age, sex [7], change in treatment during study enrollment (as a binary variable), disease etiology [81,82], duration of symptoms prior to study enrollment, previous condition specific surgery [81], and baseline instrument score. To retain adequate power for linear mixed modeling, only covariates that are correlated to the outcome measure of interest (*r* ≥ .3, by Pearson or point-biserial correlation, as appropriate) will be retained. Covariates found to be significantly correlated will be added to the relevant model in a stepwise fashion in the aforementioned order.

All outcome variables aside from VAS pain (pain severity, physical function, QoL, depression symptoms, trait mindfulness, and reinterpretation of pain) will be analyzed using linear mixed modeling with maximum likelihood estimation of missing data to compare mean change between the MBI + TAU and TAU groups’. Next, we will evaluate associations between pain, physical function, QoL, depression symptoms, trait mindfulness, and reinterpretation of pain in relation to time spent practicing mindfulness amongst participants in the intervention group. The same approach will evaluate for significant differences in RMS and RMS-peak time within sEMG findings from baseline to follow-up. Finally, we will evaluate the association between changes in RMS from baseline to follow-up and change scores of the ODI, VAS, and PD-Q in participants in the intervention group.

For all models, we will complete a modified intention-to-treat analysis (mITT) including all those participants who completed the program. A per-protocol structure using only those participants in the treatment group who completed a minimum of 5 sessions synchronously will be used for sensitivity analysis as has been used previously in clinical trials and trials of MORE [41,83,84].

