This study is limited in its participant diversity. As not all study questionnaires are available or validated in other languages, this study does not allow for the recruitment of non-English speaking participants. Similarly, Portland, OR is a majority white metropolitan area and racial diversity is limited. A second limitation is the varying sampling rate of the sEMG sensors used. This study was designed to use available equipment at the Helfgott Research Institute; ideally, all sensors used would have a minimum sampling rate of 1024 samples/second and be capable of collecting power spectrum data such as median and mean power frequency [86]. Challenges of this study reside in the evaluation of the data due to the novel nature of the study. Aspects of this study such as sEMG effectiveness in pre/post-intervention have limited literature and may present unique challenges in analysis and data collection. COVID-19 may also present additional challenges in recruitment with participants unwilling to adhere to COVID-19 guidelines or uncomfortable coming into a public space for their baseline and follow-up visits. Lastly, the large cohort sizes used in this study, 12–23 participants per group, are greater than the reported optimal group sizes for active psychotherapy interventions, 6–15 [38,[87], [88], [89], [90]]. Financial and time limitations associated with the study setting lead to need for a condensed recruitment timeline that favored fewer, larger cohorts compared with the optimal scenario of more cohorts that were smaller in group size. Future studies will likely benefit from optimal group/cohort sizing to maximize therapeutic benefit.

This study explores a distinct MBI that has not been previously investigated in this format nor with this specific subpopulation, it and responds to the existing need for more research in the effectiveness of MBI subclasses. Results gleaned from this RCT will provide valuable information regarding the relationship between chronic pain and mindfulness within the LR subpopulation. Finally, this novel area of research will provide direction for both future academic and clinical pursuits among patients experiencing chronic neuropathic pain.

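### Simple randomisation does not guarantee the stated group sizes, and the 80% power assumes no correlation within the MORE groups

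*Protocol article*

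**What the plan says.** **Allocation.** Section 3.3, on randomization and blinding, sets the method as follows: "Cohorts of 24–46 (12–23 per group) participants are recruited into the study and undergo group assignment via simple randomization using a random number generator". The same section adds that "a new random sequence is generated for each cohort" and that the coordinator assigns from a list of anonymised IDs for the cohort. Power and sample size calculations (3.7) plans 30 per group.

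**Delivery.** Intervention (3.4) describes weekly virtual sessions in which participants are asked "to engage in reflection and discussion exercises with other study participants". It refers to one instructor: "The planned MORE instructor for this trial has delivered other mindfulness interventions". The usual-care arm has no sessions during the trial and "starts their 8-week enrollment period on the same day as the experimental group" (Study design, 3.2).

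**Power.** Section 3.7 uses a t-test with alpha 0.05, d = 0.83 and 80% power. This gives 48 participants, or 60 after allowing for 80% retention. It mentions no within-group correlation.

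**Analysis.** Statistical analytical plan (3.8) specifies "linear mixed modeling with maximum likelihood estimation of missing data to compare mean change between the MBI + TAU and TAU groups" and an ordered covariate list. Neither cohort nor MORE group is on that list, and the random effects are not described. Cohort enters only to set day 1 of the daily VAS growth curve.

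**Group size.** The Discussion acknowledges that "the large cohort sizes used in this study, 12–23 participants per group, are greater than the reported optimal group sizes", as a matter of therapeutic benefit.

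**The concern.** There are two separate issues.

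First, the two ends of the per-group range are exact halves of the two ends of the cohort range, which presupposes an even split. Simple randomisation leaves the split to chance. Group size matters by the authors' own account, because they already regard these groups as larger than optimal, and an overshoot in one cohort makes that worse.

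Second, people who take a course together, talk to each other and share an instructor may have correlated outcomes. Only the MORE arm is grouped, so the design is partially nested. If the correlation is positive, a test on independent participants understates the standard error. Part of what made one course go well or badly would then be read as an effect of MORE, with too narrow an interval. The 80% power would hold only at zero correlation.

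**Working it through.** **Inputs.** From the article: cohorts of 24–46, 12–23 per group, 60 enrolled, 80% retention, d = 0.83, alpha 0.05. Assumed: ICC of 0.01, 0.02 and 0.05, and two cohorts. Two cohorts of 30 give 15 enrolled per MORE group, and 15 × 0.8 = 12 analysed. The value d = 0.83 is taken as stated; whether it follows from its inputs is a separate question.

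**1. The plan's own figure.** A two-sided two-sample t-test (noncentral t) at d = 0.83 needs 23.8, so 24 per arm, 48 in total, with power 80.4%. Then 48/0.8 = 60. Both stated figures reproduce, with independent participants and no allowance for grouping.

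**2. Group sizes under simple randomisation.** The number in one arm is Binomial(N, 0.5).

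| Cohort size | P(both arms within 12–23) |
|---|---|
| 24 | 16% |
| 30 | 80% |
| 34 | 94% |
| 36 | 93% |
| 46 | 12% |

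At 24 and 46 only an exact even split fits. For 60 overall, P(30/30) = 10%, P(35/25 or worse) = 25%, and the 95% range for one arm is 22–38. The power cost is small. With 48 analysed, power averages 79.5% over simple randomisation, against 80.4% at 24/24; at 20/28 it is 79%.

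**3. Leaving out a cohort effect shared by both arms.** Two cohorts of 24 were simulated under the null with an unadjusted t-test (20,000 runs per setting). Under simple randomisation, type I error was 4.8–5.1% for a shared cohort ICC of 0 to 0.20, so the test stays valid. With an exact half split in each cohort and cohort still omitted, it fell from 5.0% at ICC 0 to 3.9% at ICC 0.20. The test then becomes conservative, which is the reason to include cohort once allocation is restricted.

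**4. Correlation within MORE groups only.** With m = 12 analysed per group and 24 per arm:

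- Design effect in the MORE arm: DE = 1 + (m − 1) × ICC = 1 + 11 × ICC.
- True SE ÷ unadjusted SE = √((DE + 1)/2).
- Type I error of the unadjusted test ≈ 2 × (1 − Φ(1.96 ÷ ratio)).
- Adjusted power: noncentral t, 46 degrees of freedom, effect 0.83 ÷ ratio.

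| Assumed ICC | DE | SE ratio | Type I error, unadjusted test | Power after adjustment |
|---|---|---|---|---|
| 0 | 1.00 | 1.00 | 5.0% | 80% |
| 0.01 | 1.11 | 1.03 | 5.6% | 78% |
| 0.02 | 1.22 | 1.05 | 6.3% | 76% |
| 0.05 | 1.55 | 1.13 | 8.3% | 70% |

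A simulation of the unadjusted t-test with two cohorts of 24 agrees: 5.7%, 6.2% and 8.1% at ICC 0.01, 0.02 and 0.05.

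The last two columns describe different tests. The type I error belongs to the unadjusted test. The power belongs to a test whose standard error has been corrected. That power still uses 46 degrees of freedom; an analysis that counted only two MORE groups would have far fewer, so its power would be lower.

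**The case against.** **The correlation is unknown and may be small.** This stands. The article gives no ICC. A set manual, guided meditation, optional discussion, home practice from recordings and one planned instructor could all limit it. At ICC 0.01 the effect is minor. The second issue is therefore conditional, and a reader should not infer that the standard errors are certainly wrong.

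**Separate randomisation by cohort does not in itself require cohort in the model.** This also stands. Simple randomisation repeated per cohort places no constraint within cohorts and is equivalent to one overall simple randomisation. Step 3 shows that leaving out a shared cohort effect does not inflate type I error; it costs precision at most.

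**The stated group sizes may often be met.** This is true for mid-size cohorts. A reader might infer that the sizes will not be delivered, but the supportable claim is that they are not guaranteed. The article may also be using the term simple randomisation loosely for an even split, in which case the wording needs correcting.

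**Larger figures are tempting.** Setting m = 23 with ICC 0.05 gives 62% power and 11.5% type I error. But 23 in one group with 24 analysed in the arm leaves a second group of one, and 23 is an enrolled size (23 × 0.8 is about 18 analysed). Those extremes do not fit the plan.

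**The model may be fuller elsewhere.** Random effects could be set in an analysis plan not shown here, so the absence of a grouping term from the models is less firm. The allocation method and the basis of the power calculation are stated in this article, and on those the point is firm.

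**Conclusion.** The point holds in two limited parts.

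- **Allocation.** The stated method does not secure the stated sizes, least of all at the ends of the cohort range (16% at 24, 12% at 46). The consequence is mainly practical, in course sizes, since the power loss is about 1 point. This part needs no assumption beyond the article's own figures.
- **Power and precision.** The 80% holds only if outcomes are uncorrelated within MORE groups. For assumed ICCs of 0.01–0.05 and two groups of 12 analysed, the true standard error is about 3–13% larger than an unadjusted analysis would report, type I error is about 5.6–8.3%, and adjusted power is about 78–70%, or lower once the few group-level degrees of freedom are counted. At zero correlation nothing changes.

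A reader might take a cohort term as the cure for the clustering. It is not: it removes what both arms of a cohort share, whereas the correlation at issue exists only in the MORE arm.

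**What to change.** 1. Randomise each cohort by a random permutation of its ID list with exactly half to each arm (for an odd number, the extra place at random). If the whole list is assigned together, as the article suggests, an exact split adds no predictability.
2. With that restricted allocation, include cohort as a fixed effect in the between-arm models. State that this is for precision and to match the randomisation, not a correction for clustering in MORE.
3. Restate the power as 80% assuming no within-group correlation, and about 78–70% for assumed ICCs of 0.01–0.05 with groups of 12 analysed.
4. About two MORE groups can barely estimate an ICC. Report the primary interval as planned and also widened for assumed ICCs of 0.01, 0.02 and 0.05. With equal arms and groups of 12 the factors are about 1.03, 1.05 and 1.13; recompute them from the sizes achieved.

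The cost is one model term (one or two degrees of freedom), a few extra lines in the results and a less favourable power statement. The same random number generator and ID list serve.

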### Intervention

3.4

Participants randomized to the intervention group undergo an 8-week mindfulness training program as instructed by the “MORE for the Treatment of Chronic Pain” manual. The intervention consists of weekly virtual sessions during which participants are asked to follow along with a guided meditation read by a trained MORE instructor and to engage in reflection and discussion exercises with other study participants. MORE instructors are trained via a two-day intensive workshop, the only education in MORE available at the time of this publication. The planned MORE instructor for this trial has delivered other mindfulness interventions such as Being Present 2.0 [44] and is certified in delivery of Cultivating Emotional Balance. All sessions are conducted using the virtual conference platform Zoom®; session topics are outlined in Table 2. The main techniques of MORE, mindfulness, reappraisal, and savoring, are delivered in session 1, 3, and 4. Mindfulness within MORE prompts participant awareness of pain oriented attention; reappraisal asks participants to “consider new ways of thinking about a stressful situation; ” and savoring encourages participants to direct attention towards rewarding experiences [45].

**Table 2 tbl2:** MORE session topics.

Session 1	What is Pain and Why Can Mindfulness Help?
Session 2	Automaticity in Chronic Pain
Session 3	Mindful Reappraisal
Session 4	Mindful Savoring
Session 5	Relationship between Pain and Unhealthy Coping Habits
Session 6	The Stress Response to Pain
Session 7	Pain and Thought Suppression
Session 8	Review and Discussion of Maintaining a Mindfulness Practice

To maintain anonymity, participants chose a “screen name” at their baseline study visit that is associated with them at session log in and participants were encouraged, not required, to participate in group discussion using their camera and microphone. Participants in the intervention group complete weekly activities and daily guided mindfulness practices via pre-recorded MP3 files at home consistent with the MORE protocol [34]. Audio from the synchronous sessions is recorded and stored securely for participants absent from synchronous sessions. Participants who do not attend sessions without providing advance notice to the study team will be contacted using the combination of communication methods to which they indicated they preferred at the baseline visit (i.e. phone, text, or e-mail). Attempts to contact the participant will be made until the participant has reached the maximum allowed number of missed sessions, at which point they will be declared lost to follow up. In addition to completing a daily VAS and reporting treatment changes, MORE participants are also asked to report their daily time spent practicing mindfulness. All adverse events occurring during the study, including those observed by or reported to the research team, will be recorded.

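### Session non-attendance in the MORE arm is labelled loss to follow-up, which risks attendance-related missing outcomes in one arm only

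*Protocol article*

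**What the plan says.** The rule is in section 3.4 (Intervention) of the protocol article. It opens with its scope: "Participants who do not attend sessions without providing advance notice to the study team will be contacted", by whichever means the participant preferred at baseline. Attempts go on until the participant reaches "the maximum allowed number of missed sessions, at which point they will be declared lost to follow up". The article does not give the maximum.

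Only one arm has sessions. Section 3.4: "Participants randomized to the intervention group undergo an 8-week mindfulness training program". Section 3.2 (Study design): "The control group undergoes TAU over 8 weeks of parallel group comparison".

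Outcomes are collected separately from the sessions. Section 3.3 (Randomization and blinding): "Enrollment concludes at their follow-up visit within 6 weeks after the end of their 8-week reporting (intervention) period". The same section adds: "Participants unable or unwilling to complete an in-person follow-up visit are provided with the option to complete the questionnaires virtually".

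Section 3.8 (Statistical analytical plan) sets the main analysis: "we will complete a modified intention-to-treat analysis (mITT) including all those participants who completed the program". The sensitivity analysis is per protocol, "using only those participants in the treatment group who completed a minimum of 5 sessions synchronously".

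**The concern.** Stopping an intervention and being lost to outcome assessment are different events. A person who no longer joins a weekly video session may still answer an online questionnaire. Section 3.4 lets the first event stand for the second.

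This matters for the comparison because attendance arises after randomisation and exists in one arm only. If low attenders leave the MORE data while every kind of TAU participant stays in, a selected group is compared with an unselected one. Should low attenders tend to do worse, MORE looks better than it is.

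The planned mixed model with maximum likelihood does not remove the problem by itself. It is valid if missingness depends only on observed data in the model. Attendance is not among the covariates listed in section 3.8. For a declared-lost participant, the model would have to assume an outcome like that of comparable attenders, and data that were never collected cannot test this.

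**Working it through.** **1. What triggers loss, by arm.**

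| | MORE | TAU |
|---|---|---|
| Sessions during the 8 weeks | Yes (3.4) | None (3.2) |
| Can reach the missed-session limit | Yes | No |
| Follow-up visit after the 8-week period | Yes (3.3) | Yes (3.3) |
| Virtual questionnaires offered | Yes (3.3) | Yes (3.3) |

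The last two rows do not depend on sessions, so the assessment could be sought from non-attenders. No text extends the virtual option to people already declared lost.

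**2. The plan's own sample size.** Inputs from section 3.7: d = 0.83, alpha 0.05 (taken as two-sided), power 80%, retention 80%. A two-sample t-test (noncentral t) needs 23.8, so 24 per arm, or 48 in total. Power at 24 v 24 is 80.4%. Then 48 / 0.80 = 60. Both stated figures reproduce.

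**3. Effect on power.** Planned losses are 60 - 48 = 12. In the extreme case all fall in MORE, leaving 30 - 12 = 18 against 30. The noncentrality is 0.83 / sqrt(1/18 + 1/30) = 2.78, against 0.83 / sqrt(1/24 + 1/24) = 2.88 as planned. Power is 77.8% against 80.4%, a small loss.

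**4. Effect on bias.** Let a share q of MORE be declared lost, with a mean change g SD worse than that of attenders. If attenders have mean m, the whole arm has mean m - q x g. Analysing attenders only therefore overstates the MORE mean by q x g. Neither q nor g is in the documents; both are assumptions. The type I error is for a two-sided 5% t-test with no true effect, 30(1 - q) in MORE and all 30 in TAU. Points on the Oswestry Disability Index (ODI) use the SD of 8.3 from section 3.7.

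| q (people of 30) | g | Bias q x g (SD) | ODI points | Share of d = 0.83 | Type I error |
|---|---|---|---|---|---|
| 10% (3) | 0.25 | 0.025 | 0.2 | 3% | 5.1% |
| 20% (6) | 0.5 | 0.10 | 0.8 | 12% | 6.5% |
| 30% (9) | 0.5 | 0.15 | 1.2 | 18% | 8.1% |
| 40% (12) | 0.8 | 0.32 | 2.7 | 39% | 18.3% |

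The top row of q, 12 people, equals all the losses that the plan allows for, so the range does not exceed the stated retention. These are complete-case figures. Maximum likelihood would recover part of the bias only to the extent that loss depends on data in the model.

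**5. Link to the analysis set.** On its plain reading, the main set in section 3.8 leaves out people who did not complete the program, whether or not their outcomes were collected. Correcting section 3.4 alone would not change the main estimate. Correcting section 3.8 alone would leave outcomes that were never sought.

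**The case against.** The strongest reply is that the rule is narrower than it first looks. It covers unannounced absences and follows repeated outreach by the participant's preferred means. Some of these people will be truly unreachable, and for them the label is right. Session recordings are also kept for absentees. This stands, and it limits how many people the rule could affect. It does not change the trigger: as worded, the label follows from the session count.

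A reader might infer that the plan withholds the follow-up assessment from these participants. The article does not say so. Nor does it say that the daily pain prompts stop, and the virtual option in section 3.3 is not restricted by arm or attendance. Withheld assessment is an inference from the label and the end of contact attempts. The full protocol may settle the matter. If these people are in fact assessed, the sentence mislabels them and still needs correcting.

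A reader might also infer that the rule makes missingness depend on response. It makes missingness depend on attendance. The link from attendance to response is plausible but assumed, and if people stopped attending because they felt better, the bias would run the other way.

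Finally, a reader might deduct declared losses first and then apply 80% retention to the rest, for example 30 x 0.7 x 0.8 = 16.8 analysed in MORE. Section 3.7 gives 80% as overall retention, so people declared lost already belong to the 20%. That sum counts attrition twice.

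**Conclusion.** The point holds as a risk created by the wording. The rule ties loss to follow-up to attendance after randomisation, in the one arm where attendance exists, although outcomes can be collected without it. The main harm is bias rather than power.

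The size cannot be derived from the documents. Over the assumed ranges the bias is about 0.03-0.32 SD, and at the low end it is negligible. It should not be added to any bias estimated for the completer-only analysis set, because the same people are involved. The sample size of 60 is not in question here.

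**What to change.** In section 3.4, state that participants who reach the missed-session limit are recorded as non-adherent to the intervention and remain in the study. They keep receiving the daily VAS prompts and are invited to the follow-up assessment, in person or virtually, on the same schedule and with the same contact attempts as TAU participants. In both arms, use loss to follow-up only for people who cannot be reached for that assessment or who decline it.

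In section 3.8, change the main analysis set from program completers to all randomised participants by assigned arm. The per-protocol analysis can stay as a sensitivity analysis.

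The cost is two wording changes and a few more reminder messages. The virtual questionnaire route already exists, N = 60 is unchanged, and no treatment is altered. The change is best made before further cohorts reach follow-up, since outcomes not sought in the window cannot be recovered later.
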